## 1 Introduction

Type 1 diabetes (T1D) affects around 400,000 people in the UK and is caused by nearly complete loss of insulin-producing cells in the pancreas. It is often challenging to achieve good control of blood glucose throughout the day in T1D, in part because of fluctuations associated with giving insulin. Severe episodes of low blood sugar levels, commonly called “hypos”, are one of the most feared complications of managing diabetes with insulin.

The impaired release of other hormones, such as plasma glucagon which raises blood sugar, during hypo episodes is also part of type 1 diabetes. A better understanding of this mechanism could lead to treatments aimed at reducing the risk of hypoglycaemia.

Glibenclamide is an oral anti-diabetic medication (sulfonylurea) which is commonly used to increase the amount of insulin released by the pancreatic beta-cells. Recent pre-clinical studies have shown that sulfonylureas can also improve plasma glucagon levels when used in very small doses by working on pancreatic alpha-cells, which release plasma glucagon. We have previously conducted a pilot study (LEGEND-A), which suggested that low doses of glibenclamide (0.3mg/day) could alter plasma glucagon release in some people with type 2 diabetes without increasing the risk of hypoglycaemia. In addition, another type of oral anti-diabetic medication, called dapagliflozin, has also been shown to work on pancreatic alpha-cells.

Therefore, the aim of this follow-up study (LEGEND-D) is to find out whether similar doses of glibenclamide or a single dose of dapagliflozin could increase plasma glucagon release in people with T1D. We hope that add-on therapies such as these may become a new way of helping people with T1D to prevent hypoglycaemia.

The trial will involve 2 groups of participants:

- a) 20 people with T1D, who will be given a liquid form of glibenclamide orally for a maximum of 54 days (at 3 different doses, in 3 blocks of 14-18 days), followed by a single oral dose of dapagliflozin, and undergo 5 controlled hypoglycaemia challenges.
- b) A control group of 10 people without diabetes, who will undergo one hypoglycaemia challenge without receiving any medication.

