During these challenges, we will gradually drop participants' blood sugar from a normal level (around 6 mmol/L) to a lower level (around 2.5mmol/L) for 40 minutes. While this is a well-established procedure, this change in blood sugar can be stressful and participants without diabetes will probably not have experienced the symptoms before. We will screen all participants for high risk conditions, and monitor them closely during

the entire procedure. We will use a continuous glucose monitor during the study in participants with T1D. All participants will need to attend the OCDEM Clinical Research Unit at the Churchill Hospital, Oxford for an initial screening visit. This will be followed by 8 study visits over a period of 8-10 weeks (divided into around 2-week blocks) for the people with T1D, and the people without diabetes will have just 1 study visit.

The purpose of this statistical analysis plan (SAP) is to outline the planned analyses to be performed in the LEGEND-D trial. The SAP will be amended if changes to the planned analyses are required, and will be finalised before the database lock for this study. Exploratory post-hoc or unplanned analyses not necessarily identified in this SAP may be performed on these data as required. These analyses will be clearly identified in the statistical report for the study.

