### **1.3 Participants Identification**

#### **1.3.1 Trial Participants**

The anticipated recruitment period is 12 months; the recruitment target is 20 participants with T1D and 10 non-DM controls. The study will aim to include participants of different age groups.

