## **5 Statistical Methodology**

The statistical methodology for the main primary analysis is described below. Analyses will use the ITT population (section 3.2) for primary and exploratory endpoint(s), and safety population for safety endpoint(s). All statistical significance will be assessed using

an alpha value of 0.05 (95% confidence interval). The summary statistics and statistical estimates will be presented with one decimal place unless more decimal places are needed to interpret the data. All p-values will be rounded to 3 decimal places. All Tables and Figures documented in this SAP are shell versions of the anticipated results and output formats of the analyses to be conducted for the study.

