## 5.4 Exploratory endpoint analyses

### 5.4.1 Analysis of exploratory endpoints

1. To compare the concentration of plasma glucagon measured in pmol/L during induced hypoglycaemia (at 0, 15, 30 and 40min) in people with T1D prior to glibenclamide treatment, and at each dose step (at 0.3mg, 0.6mg and 3mg), to that of participants without diabetes (non-DM group).

A mixed-effects model (treatment x time-point) will be used to compare plasma glucagon values at each time-point (0, 15, 30 and 40min) during the hypoglycaemic phase of the hyperinsulinaemic hypoglycaemic clamp at baseline (T1D and non-DM group) and at each dose step (T1D group only).

Post-hoc analysis will be performed which will allow pairwise comparisons between the plasma glucagon values obtained at each time-point (T1D and non-DM group, see **Table 3**).

2. To compare the proportion of change in plasma glucagon concentration from euglycaemia to hypoglycaemia at each time point (0, 15, 30 and 40min) in T1D participants prior to treatment, and at each dose step (at 0.3mg, 0.6mg and 3mg) of glibenclamide, to that of participants without diabetes (non-DM group).

We will calculate the proportion of increase in plasma glucagon at each time point by taking plasma glucagon values at each time-point (0, 15, 30 and 40min) during the hypoglycaemic phase of the hyperinsulinaemic hypoglycaemic clamp divided by the value at the corresponding time-point during the euglycaemic phase.

A mixed-effects model (treatment x time-point) will be used to compare the proportion increase in plasma glucagon as dependent variable (i.e. plasma glucagon concentration during the hypoglycaemic phase vs plasma glucagon concentration during the euglycaemic phase) at each time-point (0, 15, 30 and 40min) as independent variable at baseline (T1D and non-DM group) and at each dose step (T1D group only).

Post-hoc analysis will be performed which will allow pairwise comparisons between the plasma glucagon values obtained at each time-point (see **Table 3**).

3. To compare the percentage of time spent in hypoglycaemia

**Table 1** (<4.0mmol/L of blood glucose) at each dose step (at 0.3mg, 0.6mg and 3mg) of glibenclamide, compared to baseline (T1D group only). Three separate paired t-tests will be used to compare 0mg vs 0.3mg, 0mg vs 0.6mg and 0mg vs 3mg. If the assumptions of t-test are not satisfied, then the percentages will be treated as proportion and a 2 proportions test will be used.

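### The fallback test for percentage of time in hypoglycaemia drops the within-person pairing and has no defined denominator, so its result depends on an arbitrary choice of unit (exploratory objective 3 only)

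*SAP*

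**What the plan says.** The endpoint is introduced in SAP section 5.4.1, item 3: "To compare the percentage of time spent in hypoglycaemia", defined there as blood glucose below 4.0 mmol/L, in the T1D group only. The main analysis keeps the pairing: "Three separate paired t-tests will be used to compare 0mg vs 0.3mg, 0mg vs 0.6mg and 0mg vs 3mg". The rule at issue follows directly. Should the t-test assumptions fail, "then the percentages will be treated as proportion and a 2 proportions test will be used".

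The glucose data come from a sensor (section 1): "We will use a continuous glucose monitor during the study in participants with T1D". Section 1.3.1 gives the number of people ("the recruitment target is 20 participants with T1D and 10 non-DM controls"), and section 1 gives the length of the dosing steps ("in 3 blocks of 14-18 days").

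The SAP does not say what the numerator and denominator of the proportion would be, how the pairing would be kept, or how the t-test assumptions would be checked. Section 6.2 identifies no transformations, section 5.4.2 plans no sensitivity analysis for exploratory endpoints, and section 4.2 makes no multiplicity adjustment.

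**The concern.** A percentage of time is a continuous measurement between 0 and 100, with one value per person per step. A two-proportion test compares counts of independent yes/no events in two independent groups. Using it here has three consequences.

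- It discards the pairing on which the main analysis of the same endpoint relies.
- It derives the variance from p(1 − p)/N, where N is a number the analyst has to choose. The observed variation of the within-person differences, which carries the real uncertainty, plays no part.
- If sensor readings are the unit, successive readings from one person are treated as independent.

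Non-normal differences are a reason to use another paired method. They do not turn a percentage into a binomial count.

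At stake is the answer to exploratory objective 3: whether time in hypoglycaemia changes on each dose. The same data could give no difference or a strongly significant one, depending on a denominator chosen after the data are in. No other planned analysis of this endpoint would expose that.

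**Working it through.** **The plan's own figure.** There is none to reproduce. The only sizing statement (section 1.3.4) concerns plasma glucagon, so the spread of time in hypoglycaemia has to be assumed.

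**Inputs from the SAP.** 20 T1D participants; 5% dropout (section 1.3.4), hence 20 × 0.95 = 19 pairs; steps of 14 to 18 days; significance at "an alpha value of 0.05 (95% confidence interval"), taken as two-sided because the SAP does not say.

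**Inputs assumed.** Level and spread of time below 4.0 mmol/L, within-person correlation, and reading interval. One reading every 15 minutes for 14 days gives 14 × 24 × 4 = 1,344 per person. Hourly units give 14 × 24 = 336, and six-hour blocks give 14 × 4 = 56.

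**Step 1: why the unit decides the result.** Take 20 pairs, mean 6%, between-person CV 0.5 (SD 3 points) and correlation 0.5.

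- Actual standard error of the mean paired difference: 3 × √(2(1 − 0.5)) / √20 = 3 / 4.472 = 0.67 points.
- Standard error used by the two-proportion test: √(2 × 0.06 × 0.94 / N) = √(0.1128 / N), with N = 20 × units per person. It rejects when the difference exceeds 1.96 times this.

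| Units per person | N | Rejects beyond (points) | In actual standard errors | Approximate type I error | Simulated (4,000 trials) |
|---|---|---|---|---|---|
| 1 (participant) | 20 | 14.7 | 21.9 | 0% | 0% |
| 14 | 280 | 3.93 | 5.9 | 0% | 0% |
| 56 | 1,120 | 1.97 | 2.9 | 0.3% | 0.7% |
| 336 | 6,720 | 0.80 | 1.2 | 23% | 22% |
| 1,344 | 26,880 | 0.40 | 0.6 | 55% | 56% |

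With participants as the unit, a mean of 6% would have to move by almost 15 points to be detected. With readings, 0.4 points suffices, which is less than one actual standard error.

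**Step 2: a skewed model.** 19 pairs, log-normal percentages with median 5%, log-SD 0.6 between and 0.4 within person, 4,000 trials per setting. Each test is run on its own.

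| Test | Type I error | Power, 30% reduction | Power, halving |
|---|---|---|---|
| Two-proportion, participants | 0% | – | 0% |
| Two-proportion, 56 units | 3.9% | 50% | 97% |
| Two-proportion, 336 units | about 40% | – | – |
| Two-proportion, 1,344 units | about 67% | – | – |
| Paired t-test | 3.9% | 59% | 97% |
| Wilcoxon signed-rank | 4.6% | 67% | over 99% |

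**Step 3: the rule as a two-step procedure.** The SAP runs the t-test unless its assumptions fail. With an assumed Shapiro-Wilk check at 0.05 on the paired differences, the fallback is triggered in about 44% of null trials. Overall simulated type I error is about 24% with 336 units and 35% with 1,344.

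A rough check treats the trigger as independent of the test result:

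- 336 units: 0.44 × 0.40 + 0.56 × 0.039 = 0.20
- 1,344 units: 0.44 × 0.67 + 0.56 × 0.039 = 0.32

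The simulated values are somewhat higher because the trigger and the test result are not independent.

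**Step 4: sensitivity to the assumptions.** A second model used beta-distributed percentages and 20 pairs, with means 3%, 6% and 10%, CV 0.5 and 0.8, and correlation 0.3, 0.5, 0.7 and 0.9 (3 × 2 × 4 = 24 null scenarios).

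- Two-proportion test, 1,344 units: type I error from 5.8% (mean 3%, CV 0.5, correlation 0.9) to 82% (mean 10%, CV 0.8, correlation 0.3).
- Two-proportion test, participants: 0% in all 24.
- Paired t-test: 4.2% to 5.8%.
- Wilcoxon signed-rank: 4.3% to 5.8%.

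**The case against.** The endpoint is exploratory, in a pilot trial, and does not feed the primary endpoint, its tests or the sample size. The named analysis is a paired t-test, which respects the design and holds its level in every setting above, including the skewed one. The disputed test is conditional, so its stand-alone error rates overstate what the SAP's procedure would produce: 35% rather than 67% in the worst case of the skewed model. All of this stands, and it limits the weight of the point.

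Four stronger readings are tempting, and the SAP does not support them.

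- A reader might infer that the fallback must give either no power or a very high false-positive rate. An intermediate unit, such as 56 blocks per person, gives 3.9% type I error and reasonable power in the skewed model. That is by accident of the denominator, since the same 56 units give 0.7% in the setting of step 1.
- A reader might infer that only participants or sensor readings could serve as the denominator. Days or blocks of hours are equally open, because nothing is specified.
- A reader might infer that skewed percentages make the planned t-test unsound. The t-test depends on the within-person differences, and it held its level here.
- A reader might treat this as a fault in the safety analysis. Sections 1.1.3, 2.2.2 and 5.4.4 define safety by adverse events, and time in hypoglycaemia is not among them.

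None of this makes the fallback valid. No choice of denominator restores the pairing or turns one percentage per person into independent counts, and no other section of the SAP qualifies the rule.

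**Conclusion.** The fallback is wrong as written and should be fixed. It ignores the pairing, treats continuous percentages as independent yes/no counts, and leaves open the denominator on which its result depends. In the skewed model the two-step rule has a type I error of about 24% to 35% against a nominal 5% when hourly or 15-minute readings are counted. With participants as the unit, the fallback cannot detect even a halving.

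These sizes rest on an assumed spread, correlation, reading interval and normality check, none of which is in the SAP. They vary widely, and in some settings the inflation is small. That the result depends on the unit follows from the formula and needs none of these assumptions. The consequence is confined to exploratory objective 3, and only if the fallback is triggered. The primary analysis is not affected.

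**What to change.** In section 5.4.1, item 3, delete the two-proportion fallback and keep the paired t-test. In place of the fallback, name a paired alternative for 0 vs 0.3 mg, 0 vs 0.6 mg and 0 vs 3 mg: either the Wilcoxon signed-rank test with a Hodges-Lehmann paired difference and 95% CI, or a paired permutation test on the within-person differences. Then either state the check and threshold that trigger the switch, or report both tests whatever any assumption check shows. Replacing the t-test outright is not needed.

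The cost is a sentence or two in the SAP and slightly more analysis, with no new data and no burden on participants. One limitation should be stated: signed-rank and Hodges-Lehmann inference about location assumes roughly symmetric within-person differences. Section 1 provides for amending the SAP and for finalising it before database lock, so the change belongs before lock. If lock has passed, the replacement analysis should be identified as unplanned in the statistical report, as section 1 requires.

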**Table 1 : Definition of hypoglycaemia**

|                |                                                                                                                       |
|----------------|-----------------------------------------------------------------------------------------------------------------------|
| Level 1 | < 4.0 mmol/L (70mg/dL) = glucose alert                                                                         |
| Level 2 | < 3.0 mmol/L (54mg/dL) = clinically important hypoglycaemia                                                    |
| Level 3 | <4.0 mmol/L with severe cognitive impairment requiring external assistance for recovery = severe hypoglycaemia |

4.To compare the change in plasma glucagon from euglycaemia to hypoglycaemia in T1D participants prior to and following administration of a single 10 mg dose of oral dapagliflozin, to that of participants without diabetes (non-DM group).

5.To compare the change in plasma somatostatin from euglycaemia to hypoglycaemia in T1D participants prior to and following administration of a single dose of dapagliflozin 10mg, to that of participants without diabetes (non-DM group).

6.To characterise the development of hypoglycaemic symptoms during induced hypoglycaemia at baseline, and during each dose of glibenclamide and dapagliflozin.

7.To measure any residual C-peptide participants with T1D only.

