**Table 2.**

**Table 2 : Oral glibenclamide suspension doses and volumes**

| Total dose | Strength | AM     | PM            | Total volume over 14 days (min) | Total volume over 18 days (max) |
|------------|----------|--------|---------------|---------------------------------|---------------------------------|
| 0.3mg      | 0.6mg/ml | 0.25ml | 0.25ml        | 7ml                             | 9ml                             |
| 0.6mg      | 0.6mg/ml | 0.5ml  | 0.5ml         | 14ml                            | 18ml                            |
| 3mg        | 0.6mg/ml | 2.5ml  | 2.5ml         | 70ml                            | 90ml                            |
|            |          |        | Total: | 91ml                     | 117ml                    |

As mentioned above, for participants with T1D the final hyperinsulinaemic hypoglycaemic clamp will involve them taking a single dose of dapagliflozin 10mg orally at the start of the study visit.

The main pharmacologically relevant site of action of dapagliflozin (Forxiga, AstraZeneca), is the sodium-glucose cotransporter 2 in the proximal convoluted tubules of the kidneys. By inhibiting this transporter, the threshold for glucose reabsorption is reduced, leading to increased glucose excretion.

Dapagliflozin also leads to increased plasma glucagon secretion by acting directly on the pancreatic islet cells [2]. Plasma glucagon concentrations are increased compared to baseline 2 hour after dapagliflozin administration, and reach a peak of 79pg/ml (23.7pmol/L) after 4 hours [3].

In total there will be 8 study visits for participants with T1D and 1 study visit for the non-DM participants.

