4. To compare the proportion of change in plasma glucagon levels measured in pmol/L at each time point 0, 15, 30 and 40min, (i.e. glucagon concentration at 0min during the hypoglycaemic phase divided by the glucagon concentration at 0min during the euglycaemic phase) from euglycaemia to hypoglycaemia in T1D participants prior to and following administration of a single 10 mg dose of oral dapagliflozin, to that of participants without diabetes (non-DM group).

Plasma glucagon values at each time-point (0, 15, 30 and 40min) during the hypoglycaemic phase of the hyperinsulinaemic hypoglycaemic clamp will be divided by the value at the corresponding time-point during the euglycaemic phase. A mixed-effects model (treatment x time-point) will be used to compare the proportion change in plasma glucagon (i.e. plasma glucagon during the hypoglycaemic phase vs plasma glucagon during the euglycaemic phase) after taking a single dose of dapagliflozin (T1D group only) versus baseline/no treatment (T1D and non-DM group).

Post-hoc analysis will be performed which will allow pairwise comparisons between the plasma glucagon values obtained at each time-point.

5. To compare the proportion of change in plasma somatostatin levels measured in pmol/L at each time point 0, 15, 30 and 40min (i.e. somatostatin concentration at 0min during the hypoglycaemic phase divided by the somatostatin concentration at 0min during the euglycaemic phase) from euglycaemia to hypoglycaemia in T1D participants prior to and following administration of a single dose of dapagliflozin 10mg, to that of participants without diabetes (non-DM group).

Plasma somatostatin values at each time-point (0, 15, 30 and 40min) during the hypoglycaemic phase of the hyperinsulinaemic hypoglycaemic clamp will be divided by the value of plasma somatostatin at the corresponding time-point during the euglycaemic phase.

A mixed-effects model (treatment x time-point) will be used to compare the proportion change in somatostatin (i.e. somatostatin during the hypoglycaemic phase vs. somatostatin during the euglycaemic phase) after taking a single dose of dapagliflozin (T1D group only) versus baseline/no treatment (T1D and non-DM group).

Post-hoc analysis will be performed which will allow pairwise comparisons using correlation [7] between the plasma somatostatin values obtained at each time-point.

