## 8 Appendices

### 8.1 Appendix 1: Reporting Conventions

**Table 3 : Groups for comparison by oral glibenclamide dose in milligrams (mg)**

|     |     | non-DM | T1D |     |     |
|-----|-----|--------|-----|-----|-----|
|     |     | 0      | 0.3 | 0.6 | 3   |
| T1D | 0   | vs.    | vs. | vs. | vs. |
|     | 0.3 | vs.    | -   | vs. | vs. |
|     | 0.6 | vs.    | -   | -   | vs. |
|     | 3   | vs.    | -   | -   | -   |

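### The only model specified for dapagliflozin's glucagon effect is a hypoglycaemia/euglycaemia ratio, which on its own cannot show whether glucagon during hypoglycaemia rises

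*SAP*

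**What the plan says.** The Introduction (section 1) asks whether low-dose glibenclamide or "a single dose of dapagliflozin could increase plasma glucagon release in people with T1D". Section 1.2 likewise presents the trial as studying the effect of both drugs on glucagon while hypoglycaemia is induced. Exploratory objective 4 (section 1.1.2) is narrower: "To compare the change in plasma glucagon from euglycaemia to hypoglycaemia in T1D participants prior to and following administration of a single 10 mg dose", set against the group without diabetes.

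Section 5.4.1 item 4 turns that objective into a ratio. Each hypoglycaemic-phase glucagon value "will be divided by the value at the corresponding time-point during the euglycaemic phase", and a treatment-by-time-point mixed model compares the ratio on dapagliflozin with the untreated ratio. Item 5 repeats this for somatostatin.

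On timing, section 1.2 has participants "taking a single dose of dapagliflozin 10mg orally at the start of the study visit". It also describes the expected effect: "Plasma glucagon concentrations are increased compared to baseline 2 hour after dapagliflozin administration, and reach a peak of 79pg/ml (23.7pmol/L) after 4 hours". That sentence does not tie the rise to hypoglycaemia.

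Concentrations are modelled in the primary analysis (5.3.1) and in 5.4.1 item 1. Both cover baseline and the three glibenclamide doses. Table 3, which lists the comparisons, has no dapagliflozin row or column. Section 5.4.2 plans no sensitivity analysis for exploratory endpoints.

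**The concern.** A ratio of two values from the same clamp responds only to the difference in relative effect between the phases. If dapagliflozin raises glucagon generally, as the sentence in section 1.2 allows, and the euglycaemic samples are taken once the drug is acting, part or all of a real rise during hypoglycaemia cancels. If the euglycaemic rise is the larger one, the ratio falls although glucagon during hypoglycaemia went up.

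This ratio carries the only specified glucagon model for one of the trial's two drugs. A flat ratio could mean that the drug does nothing, or that it raises glucagon equally in both phases. For a trial interested in raising glucagon to protect against hypoglycaemia, those are different conclusions, and no planned model separates them.

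**Working it through.** **Inputs from the SAP.** Section 1.3.4 gives mean glucagon in hypoglycaemia in T1D of 5.54 pmol/L (SD 2.14), a 30% effect and 20 T1D participants including 5% dropout. The 30% is the glibenclamide effect seen in type 2 diabetes. It is used here only as a convenient size, not as an expected dapagliflozin effect.

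**Not given, so assumed.** Euglycaemic glucagon in T1D with and without dapagliflozin, and the time from tablet to euglycaemic samples.

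**The plan's own figure.** The only power statement is 80% for the primary glibenclamide endpoint; there is none for the dapagliflozin ratio. For a paired t-test (two-sided 0.05) with difference 0.30 × 5.54 = 1.662, SD of the difference 2.14 × √(2(1 − r)) and n = 19 after dropout, power is 62% at within-person correlation r = 0, 83% at r = 0.4 and 89% at r = 0.5. It reaches 80% at r of about 0.35. The stated 80% is attainable but cannot be confirmed, because no r is given. Nothing below depends on it.

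**Proportional rises.** Let the drug multiply hypoglycaemic glucagon H by (1 + h) and euglycaemic glucagon E by (1 + e). The ratio H/E is then multiplied by (1 + h)/(1 + e), whatever its untreated value. With h = 30%, H goes from 5.54 to 7.20 pmol/L, a concentration contrast of +1.66 pmol/L for every e. The ratio behaves differently:

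| Assumed euglycaemic rise e | Ratio multiplier | Ratio reads |
|---|---|---|
| 0% | 1.30/1.00 = 1.300 | +30% |
| 15% | 1.30/1.15 = 1.130 | +13% |
| 30% | 1.30/1.30 = 1.000 | 0% |
| 50% | 1.30/1.50 = 0.867 | -13% |

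**Equal additive rise.** If both phases rise by c = 1.66 pmol/L, the ratio becomes (H + c)/(E + c).
- Untreated ratio 1.25 (E = 4.43): 7.20/6.09 = 1.18, a fall.
- Untreated ratio 1.10 (E = 5.04): 7.20/6.70 = 1.075, a fall.
- Untreated ratio 1.0: no change.

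**Detection.** Simulation of 20,000 trials, n = 20, h = 30%, untreated ratio 1.4, between-person log-SD 0.37, paired tests. All SDs are assumptions.

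| Within-person log-SD | e | Concentration test significant | Ratio test significant |
|---|---|---|---|
| 0.15 | 0% | about 99.8% | about 96% |
| 0.15 | 10% | about 99.8% | about 65% |
| 0.15 | 30% | about 99.8% | about 5% |
| 0.25 | 0% | about 83% | about 58% |
| 0.25 | 10% | about 83% | about 28% |
| 0.25 | 30% | about 83% | about 5% |

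The 5% rows are the type I error rate: at e = h the ratio does not change, so there is nothing for it to detect. Even at e = 0 the ratio is less powerful, because it carries the noise of four samples where the concentration contrast carries two.

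**The case against.** **The ratio fits objective 4.** This stands. The objective concerns change from euglycaemia to hypoglycaemia, and an equal relative rise in both phases is no relative change. A null ratio then answers that objective correctly. It leaves the broader aim in sections 1 and 1.2 unaddressed.

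**Concentration is not absent from the plan.** This also stands in part. Section 2.2.1 defines exploratory endpoints as differences from baseline in measurements that include glucagon concentration, without restriction to glibenclamide. Section 5.2 summarises outcomes by treatment period. The post-hoc step of item 4 compares glucagon values without saying whether these are raw or ratios. A reader might infer that the ratio is dapagliflozin's only glucagon endpoint; these passages do not support that. It is the only *specified model*, and the general definition is not carried into 5.4.1 for this drug.

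**Timing is unknown.** If the euglycaemic samples precede any appreciable drug effect, e is near zero and little cancels. The SAP does not give the interval, so the size of the distortion cannot be stated, and the 0% and negative readings are possibilities rather than predictions.

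**Glibenclamide is not affected in the same way.** Item 2 uses the same ratio, and one might infer that a suppressed euglycaemic value could pass for a better response there. The primary analysis and item 1 already analyse glibenclamide concentrations during hypoglycaemia, so such an artefact would be seen.

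**The trial is a pilot and the endpoint exploratory.** True. Section 1 also permits further analyses if labelled as unplanned. That limits the harm, but a contrast specified in advance is worth more than one added after the ratio has been seen.

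**Conclusion.** The point holds as a gap in specification. The only model named for dapagliflozin and glucagon is a ratio whose denominator may be on drug, and by itself it cannot show whether glucagon during hypoglycaemia rises. A true 30% rise can read anywhere from +30% to -13% as the assumed euglycaemic rise goes from 0% to 50%. The cancellation is algebra; where this trial falls in that range depends on an unstated euglycaemic effect and an unstated dose-to-sample time. Item 5 has the same structure for somatostatin.

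It would be tempting to conclude that the trial cannot answer its dapagliflozin question, or that the ratio is blind to the drug. Neither follows. The item 4 ratio requires glucagon in both phases, so the needed data are due to be collected, and the ratio keeps useful power when the rise is confined to hypoglycaemia. The primary result is untouched. This is a worthwhile, inexpensive improvement to an exploratory analysis.

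**What to change.** 1. In 5.4.1 item 1, add dapagliflozin as a treatment level in the concentration model, and add it to Table 3.
2. Report dapagliflozin versus step 1 in pmol/L separately for the euglycaemic and hypoglycaemic phases, for example through a treatment-by-phase term.
3. Specify the matching concentration model by phase for somatostatin, which item 1 does not cover.
4. Keep the ratios in items 4 and 5 for objectives 4 and 5, and state that a change in ratio will be interpreted only together with the two phase-specific contrasts.
5. Reconcile section 2.2.1 with items 4 and 5, and say whether their post-hoc comparisons use concentrations or ratios.

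The cost is SAP wording and one or two extra models, with no additional sampling. The downside is a few more exploratory contrasts with no multiplicity adjustment (section 4.2), which should be reported as such.
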